#### Subject discontinuation and withdrawal

Subjects may voluntarily withdraw from study participation at any time. If a subject is removed from the study, an attempt should be made to obtain the follow-up evaluation that would have been obtained at the completion of the study, provided the patient consents to do so.

#### Risks to subjects

The risks of participating in the study are outlined in the introduction as inherent risks of delivering radiation without a pathologic diagnosis:

Creating a non-diagnostic biopsy through radiation effects on tissue.Possible increase in the risk of biopsy complications.Risk of treating a non-cancerous process.Risk of treating a cancer that would be best managed with chemotherapy/systemic therapy as the primary treatment (i.e. lymphoma, small cell lung cancer, germ cell tumor).

We will be measuring each of these risks carefully during the study to determine whether the level of risk is acceptable as a standard of care approach in this selected population. In our population, there is also a risk of *not* participating in the study: the cancer may progress and cause symptoms and complications during the waiting period for a biopsy sample.

#### Risk to subjects undergoing radiation to the only available site of biopsy

For the subset of patients with a single lesion to biopsy, the reason for urgent radiation treatment must be carefully documented and risks of non-diagnostic biopsy discussed with the patient. Any medical oncologist assigned to the patient should be consulted to determine the potential negative impacts if molecular testing is not able to be obtained. If the patient does not have an assigned medical oncologist, the treating radiation oncologist can consider reaching out to a medical oncologist specific to that disease site or the medical oncologist on call, but this is not absolutely required. There will be a safety interim analysis conducted as discussed under the planned safety interim analysis section, and if the yield of histological diagnosis is < 80% or yield of molecular testing is < 70%, then no further patients will be enrolled where the site of radiation is the site of biopsy.

#### Confidentiality of subject records and data storage

All data will be stored on REDCap, which is a secure web application for building and managing online databases commonly used in the clinical trials research community.

#### Financial support for patients

Patients are not financially renumerated on this trial.

## Discussion

This pragmatic single-arm clinical trial seeks to collect prospective data on patients with presumed metastatic (or otherwise incurable) cancer where there is an urgent need for palliative radiation. There is currently a paucity of data to guide empiric decision-making for radiation oncologists and patients in these situations. By treating all such patients with upfront palliative radiation on trial before biopsy results are available, we will prospectively measure the accuracy of modern imaging and clinical acumen in guiding radiotherapy decision-making in the palliative oncology setting. We believe that if the rate of inappropriate radiation is found to be no more than 5%, then this approach should be considered safe and feasible in the palliative setting.

RT-NOW was designed pragmatically to mimic real world practice [6] and the PRECIS-2 tool was used for trial design considerations (Fig. 2). For instance, we allowed broad eligibility across patients with different cancer histologies, performance statuses and radiation indications. Limited inclusion/exclusion criteria allowed treating physicians to consider the nuances specific to each patient, scenario and cancer type. We only requested that physicians need to be quite certain (> 95% likelihood) they are treating an incurable malignancy (based on available investigations) and that the risks of delaying radiation outweigh the risks of upfront radiation. There were no recruitment efforts beyond usual care. Radiation treatment schedules and techniques were decided by the treating physician, again reflecting our pragmatic approach. In addition, the limited number and scope of study follow-up visits was intended to mimic real-life practice in the palliative settings and the burden on patients and their caregivers. These patients often have limited life expectancies, and we do not want to overburden them with additional appointments. In addition, we chose the validated ESAS questionnaire to assess patient’s symptom burden and quality of life, given its ease-of-use, brevity and ability to add additional symptoms most specific to the patient [8].

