## Methods

### Objective

To determine if it is safe and feasible to deliver palliative radiation before a biopsy result is available in a carefully selected group of patients with urgent indications for radiation.

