### Statistics and sample size calculations

We hypothesize that the primary endpoint, rate of “inappropriate radiation”, will be no more than 5%. We consider it unacceptable if the rate of “inappropriate radiation” is ≥ 20%. Using a one-sided, one-sample binomial test, with 90% power at the 5% significance level, to reject the null hypothesis of a change rate of ≥ 20%, with 10% drop-out, we estimate that 48 patients are needed.

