### Data analysis

Patients who decline a biopsy after RT will be excluded from analysis of both primary and secondary endpoints. Patients for whom biopsy is repeatedly non-diagnostic after undergoing RT will be masked from analysis of the primary endpoint, since inappropriate use of RT cannot be determined without a biopsy. However, analysis of secondary endpoints will be conducted, including determination of overall rates of diagnostic yields/accuracy, complications from biopsy, and number of biopsy attempts.

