**Fig. 2 Fig2:**
[figure not shown]
PRECIS-2 wheel for RT-NOW trial

One of the main risks of this study is the downstream impact a non-diagnostic biopsy may have on available systemic therapy options for the patient, especially in the era of targeted agents and immunotherapy. For example, it would be a significant error if pre-emptive radiotherapy to the biopsy site led to a non-diagnostic result in a patient that would have been eligible for life-prolonging targeted therapy. In patients with several sites feasible to biopsy, these risks are minor, as an unirradiated site may be biopsied even if the initial biopsy of an irradiated site was non-diagnostic. In that situation, the only harms would be the inconvenience and risks associated with an additional biopsy procedure. However, in patients with only one feasible site to biopsy, if radiation was to render the biopsies non-diagnostic, a successful re-biopsy may only be possible at disease progression. Given the risks unique to this set of patients, we will collect data on biopsy yields prospectively and do an interim safety analysis once half the patients have been accrued and their full data are collected.

To our knowledge, there are currently no similar trials studying this question of upfront palliative radiation in patients without a biopsy. Prospective data from this trial will be valuable in helping to guide the complex decision-making of physicians and cancer patients in these urgent palliative situations.

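### The Discussion concludes safe and feasible from the inappropriate-radiation rate alone, so poor biopsy yield or more biopsy complications never count against that conclusion

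*Protocol article*

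**What the plan says.** The Objective is "To determine if it is safe and feasible to deliver palliative radiation before a biopsy result is available" in selected patients with urgent indications. The Discussion supplies the link from result to conclusion: "if the rate of inappropriate radiation is found to be no more than 5%, then this approach should be considered safe and feasible". No other sentence in the article states which result would meet the objective.

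The primary endpoint counts two kinds of event: a biopsy that clearly shows a non-malignant entity, and a malignancy for which another treatment would have come first. Under Data analysis, "Patients for whom biopsy is repeatedly non-diagnostic after undergoing RT will be masked from analysis of the primary endpoint".

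Other sections take a wider view of safety:

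- Risks to subjects lists four risks: non-diagnostic biopsy, biopsy complications, treating a non-cancerous process, and treating a cancer better managed first with systemic therapy. It then ties all four to the acceptability of routine use: "We will be measuring each of these risks carefully during the study to determine whether the level of risk is acceptable as a standard of" [...].
- The Discussion (after Fig. 2) says "One of the main risks of this study is the downstream impact a non-diagnostic biopsy may have on available systemic therapy options for the patient". It adds that this risk is minor where several sites can be biopsied and more serious where only one can.
- The Conclusions give the aim as three rates: inappropriate management, biopsy complications and non-diagnostic biopsies.
- The hypotheses under Study design set benchmarks from institutional averages: histologic yield 90–95%, molecular yield 80–90%, complications 5–10%.
- Planned safety interim analysis sets limits of 80% (histologic) and 70% (molecular) in patients whose only feasible biopsy site was irradiated. Crossing either one ends enrolment of patients whose radiation site is the biopsy site.

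**The concern.** The stated condition for the conclusion has two inputs: the number of inappropriate cases and the number of evaluable patients. Two of the four named risks are not among them. A patient whose biopsies repeatedly fail leaves the denominator and is never counted as an event. A biopsy complication, or a failed molecular test with histology obtained, does not enter at all.

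The sentence therefore conflicts with Risks to subjects and with the Conclusions. At stake is the headline claim. The trial could report the approach as safe and feasible while its own secondary results show poor diagnostic yield or more complications, and nothing written would stand against that. Patients with a single feasible biopsy site would be the most exposed to such a reading, because the article says a successful re-biopsy may be possible for them only at progression.

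**Working it through.** **1. Reproduce the plan's sample size.** Inputs from Statistics and sample size calculations: null rate 20%, hypothesised rate 5%, "Using a one-sided, one-sample binomial test, with 90% power at the 5% significance level", 10% drop-out, 48 patients. The smallest n with P(X ≤ k | 0.20) ≤ 0.05 and P(X ≤ k | 0.05) ≥ 0.90 is n = 44 with k = 4: type I error 0.044, power 0.933. Allowing for drop-out, 44 × 1.1 = 48.4, or 48 (44/0.9 = 48.9 would give 49). The planned 48 is reproduced.

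**2. Match the risks to the conclusion.**

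| Named risk | In the primary endpoint? | Other limit stated |
|---|---|---|
| Non-cancerous process | Yes | Interim stop at 5 or more of 24 |
| Cancer better treated first with systemic therapy | Yes | Interim stop at 5 or more of 24 |
| Non-diagnostic biopsy | No; masked | 80%/70%, interim, single-site subset, affects enrolment only |
| Biopsy complications | No | None; 5–10% benchmark as a hypothesis |

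**3. Stress test.** Assumptions: 43 biopsied patients (48 × 0.9 = 43.2), a true inappropriate rate of 5%, and a proportion q of patients repeatedly non-diagnostic and masked, independently of whether radiation was inappropriate. The protocol's own estimate of non-diagnostic biopsy is below 5%, so the larger values of q are deliberately severe.

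Evaluable patients m ~ Binomial(43, 1 − q); events X ~ Binomial(m, 0.05).

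- Discussion condition: P(X/m ≤ 0.05), summed over m.
- Powered test: P(X ≤ k(m)), where k(m) is the largest k with P(X ≤ k | m, 0.20) ≤ 0.05, summed over m.

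| q | Observed rate no more than 5% | Exact test rejects 20% |
|---|---|---|
| 5% | 0.62 | 0.85 |
| 10% | 0.52 | 0.85 |
| 20% | 0.49 | 0.78 |
| 30% | 0.55 | 0.71 |
| 40% | 0.62 | 0.63 |
| 50% | 0.61 | 0.52 |

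The first column falls and then rises because counts are whole numbers. With 40 to 43 evaluable patients the condition allows 2 events, and with 20 to 39 it allows 1. So P(X ≤ 2 | 43) = 0.64, P(X ≤ 1 | 34) = 0.49 and P(X ≤ 1 | 22) = 0.70. The second column falls because m shrinks. Neither column contains a judgement about yield, and the complication rate appears in neither formula.

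**4. A worse true rate.** With 43 patients and a true inappropriate rate of 10%, the Discussion condition is met with probability 0.18 at q = 0 and 0.28 at q = 50%.

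**The case against.** The strongest reply is that the Discussion sentence is an opinion of the authors and not a prespecified decision rule. The formal inference is the binomial test against 20%, and nothing makes safe and feasible the output of that test. The article also does assess the other two risks. Yield (with irradiated and non-irradiated sites compared), number of attempts, complications and radiation effect are secondary endpoints. Repeatedly non-diagnostic patients stay in those analyses, and Study design gives benchmarks. A single primary endpoint with descriptive safety outcomes is an ordinary design.

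The 50% scenario is also remote. Any site may be biopsied, a second attempt may go elsewhere, and the biopsy may precede radiation. At a true histologic yield of 50%, the interim 80% limit would be crossed with probability 0.81 with 5 single-site patients and 0.95 with 10 (subset sizes assumed; the article gives none).

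Most of this stands as a limit on the point. A reader might infer that the conclusion is reached just as often when half of the biopsies are lost. The figures do not support that: the 5% condition dips to 0.49 at 20% before recovering, and the powered test falls from 0.85 to 0.52. A reader might also infer that the trial ignores yield and complications. It does not; it measures them. What the reply does not remove is that the only sentence tying a result to the objective makes no use of those measurements, while another section says they help to decide acceptability.

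**Conclusion.** The point holds as an inconsistency between the stated conclusion and the stated risks. The Discussion's conclusion is broader than the endpoint it rests on, and it cannot be squared with Risks to subjects or the Conclusions as written. With 43 biopsied patients, a true inappropriate rate of 5% and masking unrelated to outcome, the chance of meeting the 5% condition is 0.62, 0.49 and 0.61 at 5%, 20% and 50% non-diagnostic. It varies with discreteness but carries no consistent penalty for lost biopsies. The powered test drops to 0.85, 0.78 and 0.52 at the same points, through fewer evaluable patients only. These are stress-test figures, not forecasts.

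The primary test itself is not undermined by this point. The consequence is for what the trial may claim, chiefly for patients with a single feasible biopsy site.

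**What to change.** Reword the Discussion sentence so that the primary endpoint supports only the conclusion that the rate of inappropriate radiation is acceptably low. State beside it that safe and feasible also depends on final histologic yield, molecular yield and biopsy complications. Report each with an exact confidence interval against the protocol's own benchmarks (90–95%, 80–90% and 5–10%). Show yield separately for irradiated biopsy sites and for patients with a single feasible site.

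Formal co-requirements are optional. If the sponsor wants them, it should choose limits for the final analysis and say whether the estimate or the confidence bound must meet them. The interim 80% and 70% limits were set for the single-site subset and do not transfer automatically to all biopsies of irradiated sites.

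The cost is wording only. The data are already to be collected, the sample size does not change, and no patient's treatment changes. The downside is a narrower headline conclusion, and intervals in the single-site subset may be wide.

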**Fig. 2 Fig2:**
[figure not shown]
PRECIS-2 wheel for RT-NOW trial

One of the main risks of this study is the downstream impact a non-diagnostic biopsy may have on available systemic therapy options for the patient, especially in the era of targeted agents and immunotherapy. For example, it would be a significant error if pre-emptive radiotherapy to the biopsy site led to a non-diagnostic result in a patient that would have been eligible for life-prolonging targeted therapy. In patients with several sites feasible to biopsy, these risks are minor, as an unirradiated site may be biopsied even if the initial biopsy of an irradiated site was non-diagnostic. In that situation, the only harms would be the inconvenience and risks associated with an additional biopsy procedure. However, in patients with only one feasible site to biopsy, if radiation was to render the biopsies non-diagnostic, a successful re-biopsy may only be possible at disease progression. Given the risks unique to this set of patients, we will collect data on biopsy yields prospectively and do an interim safety analysis once half the patients have been accrued and their full data are collected.

To our knowledge, there are currently no similar trials studying this question of upfront palliative radiation in patients without a biopsy. Prospective data from this trial will be valuable in helping to guide the complex decision-making of physicians and cancer patients in these urgent palliative situations.

## Conclusions

RT-NOW is a pragmatic single-arm trial studying patients who are believed to have incurable cancers, where a biopsy is delaying urgent palliative radiation. The aim of this trial is to prospectively collect data on a radiation-before-biopsy approach to determine the rates of inappropriate management, biopsy complications and non-diagnostic biopsies. Such evidence is critically needed to help oncologists and patients make informed management decisions in these urgent situations.

## Data Availability

No datasets were generated or analysed during the current study.
